### Methods in analysis to handle protocol non-adherence and any statistical methods to handle missing data {20c}

The full analysis set (FAS) will be defined according to the intention-to-treat (ITT) principle. The FAS will consist of all randomised subjects analysed according to the study arm to which they were assigned at randomisation. Participants who withdraw consent for continued follow-up will be included in the analysis by modern imputation methods for missing data as sensitivity analysis. Where possible, reasons for withdrawal for each group will be reported and compared qualitatively.

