Available data from the screening and verification visits informed the estimated total number of clusters that would be needed to reach 5400 eligible households. During the screening and verification process, BRAC Uganda found that approximately 25% of project participants were people with disabilities, and as such it was expected that the trial would include 675 people with disabilities in each arm. The distribution of eligible households per village was used to simulate the trial, 185 villages sampled with replacement from the verified villages gave approximately 5400 research participants in a simulated trial. A value of 0.8 was used from a recent evaluation of the graduation programme in Ghana for the standard deviation of the distribution of the normalised per-capita expenditure at baseline [10]. Since the degree of clustering in the outcome was unknown, the intraclass correlation coefficient (ICC) was allowed to vary between 0.05 and 0.3. The estimated between-village variation in mean level of the outcome at baseline and individual-level outcomes were drawn from the village-level means with a constant within-village variance. The endline results were generated using the simulated baseline data and a covariance matrix with a pre-post correlation of either 0.4, 0.6, or 0.8. The 185 clusters were pair-matched by the number of people with disabilities and a constant intervention effect was applied to the clusters allocated to the intervention arm. The intervention effects ranged from a difference between the intervention and control arms in the mean per-capita expenditure of zero standard deviations of the baseline per-capita expenditure, to 0.2 standard deviations, which is as high as the largest effects on per-capita expenditure observed in previous trials [1]. Multi-level linear regression was used to estimate the effects, controlling for baseline per-capita expenditure, accounting for clustering with a village-level random effect, and for the randomised design with fixed-effect for the pairs.

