### Implementation {16c}

Assignment of clusters to intervention and control arms is led by the implementing partners (BRAC, HI, and NUWODU) with support from IERC and BIGD, in order to meet the criteria for the evaluation. Allocation is conducted at one time point prior to the baseline survey and implementation of the DIG programme. The programme team pre-identified the desired number of intervention beneficiary households that each of the eight BRAC branches could support based on the sample size of 2700 households. This number ranged from 320 to 420 households.^1^ The number of eligible households, identified during the screening and verification process, within each cluster was calculated. Permutations of cluster allocation were then run in Stata, until the desired total number of 2700 households for the DIG programme was reached in the intervention arm. Remaining clusters were assigned to the control. In the end, 96 clusters were assigned to the intervention arm and the remaining 89 clusters to the control arm. Overall, 2898 households were assigned to the intervention arm while 2402 households were retained as control—the distribution of households by district and BRAC branch is shown in Table 2.

**Table 2 Tab2:** Distribution of households in control and intervention arms by district and BRAC branch

District	BRAC Branch	Number of Households		
		Control Arm	Intervention Arm	Total
Gulu	Gulu	367	355	722
	Lacor	288	340	628
	Goma	280	406	686
Nwoya	Anaka	366	370	736
Oyam	Minakulu	324	402	726
	Kamdini	285	357	642
	Loro	263	311	574
Kiryandongo	Kigumba	229	357	586
Total		2402	2898	5300

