## Statistical methods

### Statistical methods for primary and secondary outcomes {20a}

For basic description, we will report the mean and standard deviation (or median and interquartile range) for continuous variable and the number and percentage for categorical variables, by intervention status (yes or no), and by data wave (baseline vs follow-up). We will test the balance of the covariates by *t*-test (or Mann Whitney *U* test) for continuous variables and by chi-square test for any categorical variables. Covariates include socio-demographic factors (e.g., age, sex), as well as any other factors likely to affect the implementation of the intervention.

Data will be fitted with multi-level linear regression to test the effect of the intervention, with the difference of the primary or secondary outcomes between follow-up and baseline as the outcome, and intervention status as the exposure, controlling for potential imbalance in covariates at baseline. To account for the data structure, we will consider the random intercept and random slope for exposure at the level of district and pair indicators. To address multiplicity concerns the Bonferroni Correction or Bayesian modelling approaches will be applied. The model’s adequacy will be assessed through residual plots, with log transformations of variables considered if residuals are not randomly distributed. All analysis will be conducted in Stata and R. We will report the estimation as coefficient for continuous outcome and OR for binary outcome, as well as their 95% confidence interval (CI). *P* value < 0.05 will the level of statistical significance.

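### The change-score main analysis leaves out every household missing a survey, and the only stated remedy names consent withdrawers alone

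*Protocol article*

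**What the plan says.** Section {20c} sets the principle: "The full analysis set (FAS) will be defined according to the intention-to-treat (ITT) principle". It then fixes membership: "The FAS will consist of all randomised subjects analysed according to the study arm to which they were assigned at randomisation". The next sentence is its only missing-data rule: "Participants who withdraw consent for continued follow-up will be included in the analysis by modern imputation methods for missing data as sensitivity analysis". The section ends with a promise to report and compare reasons for withdrawal where possible.

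Section {20a} specifies a multi-level linear model whose dependent variable is a change score: "with the difference of the primary or secondary outcomes between follow-up and baseline as the outcome".

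No other section gives a method for missing outcomes. Section {11b} allows withdrawal without a reason, section {18b} deals with retention, and the sample size section {14} makes no allowance for loss. Under Trial design {8} and Implementation {16c}, villages were allocated before the baseline survey. Implementation {16c} gives the numbers randomised: "2898 households were assigned to the intervention arm while 2402 households were retained as control".

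**The concern.** A difference between two surveys exists only for households seen at both. The analysis set is described as everyone randomised, but the main model can use only those with complete pairs. The stated remedy does not close this gap, because it names one reason for loss.

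That reason fits this trial poorly. Under section {26a}, consent is taken afresh at each survey round, so a household that cannot be traced in October 2023 has not withdrawn anything. A household allocated but not interviewed in November 2020 has no baseline and therefore no change score, even if it is surveyed at an endline.

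What is at stake is whether the sensitivity analysis tests the right threat. From baseline there are about 20 months to endline 1 and 35 to endline 2. During the programme, the intervention arm has home visits, coaching and savings groups; the control arm has none of these. Moving away and non-contact are losses that such contact could plausibly influence. An imputation restricted to withdrawers would not show whether they matter.

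**Working it through.** **1. The plan's own figures.** Sample size {14} states that "it was expected that the trial would include 675 people with disabilities in each arm". This reproduces: 0.25 × 2700 = 675 per arm, or 1350 in all. The totals in section {16c} also agree: 2898 + 2402 = 5300 households and 96 + 89 = 185 clusters. The 675 contains no allowance for loss.

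**2. Who is in which analysis, as written.**

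| Household | Main change-score model | Stated sensitivity imputation |
|---|---|---|
| Both surveys done | in | in |
| Consent withdrawn, follow-up missing | out | in |
| Moved, dissolved or not found at endline | out | not named |
| Endline done, baseline not done | out | not named |

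**3. How many households this could be.** The article gives no attrition rate, so these are assumptions. At 5%, 10% or 20% loss by endline 2, 5300 × loss = 265, 530 or 1060 households outside the main model. Among the 1350 expected participants with disabilities, the same rates give about 68, 135 or 270.

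**4. How much the stated imputation could reach.** Let L be the share lost and w the share of losses that are consent withdrawals. Both ranges are assumed: L = 10-25%, w = 10-30%.
- Covered = L × w: 0.10 × 0.10 = 1% up to 0.25 × 0.30 = 7.5% of the sample.
- Not covered = L × (1 − w): 0.10 × 0.70 = 7% up to 0.25 × 0.90 = 22.5%, which is about 371 to 1,193 of 5300.

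**5. Possible bias.** Let a1 and a0 be the loss in the intervention and control arms, and g the number of SDs by which the change in lost households falls below that in retained ones. Each arm's retained mean is too high by a × g, so

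bias (complete cases minus all randomised) = (a1 − a0) × g.

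- 3-point difference, g = 0.3: 0.03 × 0.3 = 0.009 SD in size.
- 10-point difference, g = 0.5: 0.10 × 0.5 = 0.05 SD in size.
- 5% versus 15% loss: (0.05 − 0.15) × 0.3 = −0.03, and × 0.5 = −0.05.
- Equal loss and equal g: 0.

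Against the 0.1 SD effect in section {14}, 0.009-0.05 SD is roughly 10-50%. The sign depends on which arm loses more and on whether lost households do worse or better. If g differs by arm, the bias is a1 × g1 − a0 × g0, which need not vanish under equal loss: 10% loss in both arms with gaps of 0.5 and 0.3 gives 0.10 × 0.2 = 0.02 SD.

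Here g is a gap in change. A stable difference in level between lost and retained households cancels in a change score and causes no bias.

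**6. What the baseline-adjusted model does.** It is the model in the article's own power simulation (section {14}), and it can keep a household that lacks only a baseline. It is also more precise. With equal variance at both waves and pre-post correlation r, residual variance is 1 − r² when baseline is a covariate and 2(1 − r) for a change score:

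| r | Baseline as covariate | Change score |
|---|---|---|
| 0.4 | 0.84 | 1.20 |
| 0.6 | 0.64 | 0.80 |
| 0.8 | 0.36 | 0.40 |

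**The case against.** The best defence is that silence is being read as exclusion. Section {20c} does not say that imputation is confined to withdrawers. A short item in a journal article may leave relocation, death and non-contact to the full protocol or analysis plan. This stands in part: that other losses go unhandled is inferred. The inference is nevertheless close, because the section states a rule, its population and its status, and the change-score outcome leaves no other way in for those households.

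Three further points stand:
- Because consent is renewed at each round, a refusal at an endline might be counted as a withdrawal, which would widen the rule. A household never traced would still fall outside it.
- An available-case main analysis with imputation as a sensitivity analysis is accepted practice, and keeping imputation in that role is no fault.
- The case for unequal loss is plausible but not shown. The programme ended in June 2022, about 16 months before endline 2. The surveys in both arms are run by a group described as independent of the implementer, and the retention measures in section {18b} are not specific to one arm.

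A reader might infer that only losses other than consent withdrawal leave the main analysis. They do not support that: withdrawers leave it too, since their imputation is a sensitivity analysis. A reader might also infer that the primary result will be biased by up to half the target effect. The documents contain no attrition rate, no difference by arm and no gap, so they cannot support that either.

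**Conclusion.** The point holds in this form. The analysis set is said to contain everyone randomised. The change-score outcome removes from the main analysis every household missing either survey, and the one stated remedy names a single reason for loss. Households lost for other reasons, or missed at the post-allocation baseline, are on the text as it stands in neither analysis.

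The size of any bias is unknown. The 0.01-0.05 SD range rests wholly on an assumed 3-10 point difference in loss and an assumed 0.3-0.5 SD gap in change. Bias arises only if loss, or its relation to change in expenditure, differs between arms. Households without a person with disabilities are absent from endline 1 by design and are not missing data at that round.

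**What to change.** 1. **Main analysis.** Model the endline value with baseline as a covariate, as in the section {14} simulation, for every randomised household with an endline outcome. Fill a missing baseline by mean or indicator imputation instead of dropping the household. Since the baseline survey followed allocation, tabulate missing baselines by arm.
2. **Sensitivity analysis.** Extend the imputation from consent withdrawers to all missing endline outcomes whatever the reason, by arm and respecting clustering, and add a delta-shift (not-at-random) version. Use the pre-randomisation screening data where this is permitted: the implementer collected them, and Table 1 lists research consent only from baseline onwards.
3. **Reporting.** Give loss by reason and arm, against 2898 and 2402 at endline 2 and against the randomised households with a person with disabilities at endline 1.

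Imputation may remain a sensitivity analysis. The cost is revised wording in the analysis plan and some extra analysis. No new data collection is needed, though permission to use the screening data has to be checked.

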### Plans to give access to the full protocol, participant-level data, and statistical code {31c}

Twelve months after the end of the study, the anonymized survey data will be made available on LSHTM’s Data Compass (datacompass.lshtm.ac.uk), for which explicit consent has been included in the consent form, alongside project documentation and a data user guide.

## Oversight and monitoring

### Composition of the coordinating centre and trial steering committee {5d}

BRAC Uganda is responsible for the intervention design, allocation, implementation, and programme monitoring. BIGD and IERC lead household survey data collection, and Makerere University leads qualitative data collection for the process evaluation. Evaluation design and analysis is led by LSHTM, in partnership with BIGD, IERC, and Makerere University. Monitoring data collected from implementing partners is shared with LSHTM for the purpose of the process evaluation.

### Composition of the data monitoring committee, its role and reporting structure {21a}

As the evaluation is not blinded and the interventions pose a limited risk to participants, a data monitoring committee is not required.

### Adverse event reporting and harms {22}

Delivery of interventions is monitored by BRAC Uganda. As the intervention is targeted at the worst-off households, many households within the intervention villages do not actually receive the intervention. It is possible that the targeting methods are imperfect or appear imperfect to members of the communities, and that there is resentment within the villages. This is not a feature of the random allocation but is a feature of the programme. Resentment may lead to perpetration of violence of theft, particularly targeting people with disabilities, which is monitored by BRAC Uganda through a feedback and complaint handling mechanism, and will inform the process evaluation.

### Frequency and plans for auditing trial conduct {23}

Data is quality assured in the field by the data collection team supervisor and checked after submission by the data manager. Any discrepancies are followed up with the relevant data collector as required.

### Plans for communicating important protocol amendments to relevant parties (e.g. trial participants, ethical committees) {25}

Any important modifications to the study protocol are agreed between BRAC Uganda, Makerere University, and LSHTM, and approved by LSHTM Ethics Committee and Mildmay Uganda Research Ethics Committee prior to implementation.

### Dissemination plans {31a}

To disseminate findings from this research, we will write academic articles, present at conferences and publicise the results through our network of academic and non-academic partners.

## Discussion

The DIG programme is an ambitious attempt to deliver an intervention that aims to sustainably change the levels of poverty among people with disabilities in rural Uganda. There is currently a lack of evidence on the impact of interventions designed to improve livelihoods among people with disabilities [14]. DIG is a promising intervention to evaluate, as it has been adapted to be disability inclusive across programme components through extensive consultations and collaboration with people with disabilities, OPDs, and other disability experts. Furthermore, it has proved effective at reducing poverty among other target groups in several different contexts [1].

This is a pragmatic trial [15], where the intervention is being delivered in ‘real-life’ conditions. Pragmatic trials delivered in ‘real-life’ conditions have advantages and disadvantages for informing policy. They are inherently realistic, so any evidence of effect is a good indication that a scaled-up programme could replicate the effects. However, by being so dependent and contingent on the context at all levels, generalising the effects (or lack thereof) to other settings—or even the same setting in the future [16]—can be challenging. We are addressing this disadvantage with a theory-driven process evaluation that will identify key mediators and moderators of the processes that occurred and will combine this with other data to make recommendations on how interventions should be informed by this evaluation when delivered elsewhere.

Finally, pragmatic trials have challenges relating to the ethics of randomisation and data collection from people who are not directly receiving the intervention. Questions arise since the programme is not an intervention developed for the purposes of research about which there is ‘equipoise’, but an NGO-led programme that has been shown to be effective in other contexts. The decision to randomise was itself pragmatic; the funds were limited, and many more eligible people had been identified. More importantly for the cause of generating evidence for people with disabilities, while the intervention has been shown to be effective before it has not been for people with disabilities. Given the programme’s emphasis on inclusion, it is difficult to design an intervention that would both allow all people without disabilities to get the intervention (because it has been previously shown to be effective) but not people with disabilities (because a trial is justified by the lack of evidence). Striking the balance between the interests of generating evidence for a marginalised group and rolling out a proven approach to poverty alleviation is a challenge for this and for future research.

## Trial status

This manuscript is based on protocol version 2, 24 August 2020. Baseline data collection and recruitment was conducted in November 2020. The first endline evaluation was conducted in July 2022 and the second endline is planned for October 2023. It was not possible to submit the manuscript prior to participant recruitment as funding for the second endline was pending (now approved) and this would have influenced the study design.

## Data Availability

Twelve months after the completion of the endline data collection, the data will be made available on LSHTM’s Data Compass, along with project documentation and a data user guide. The data will be made available open access, ensuring that no identifiers are included in the data. Explicit consent has been included for making data open access.

## Abbreviations

BIGD: BRAC Institute of Governance and Development
CI: Confidence interval
COVID-19: Corona virus disease 2019
DIG: Disability-inclusive graduation programme
FAS: Full Analysis Set
FCDO: Foreign, Commonwealth and Development Office
GPS: Global Positioning System
HI: Humanity and Inclusion
ICC: Intraclass correlation coefficient
IERC: Independent Evaluation and Research Cell
ITT: Intention-to-treat
LSHTM: London School of Hygiene and Tropical Medicine
MRC: Medical Research Council
NGO: Non-governmental organisation
NUWODU: National Union of Women with Disabilities of Uganda
OPD: Organization of persons with disabilities
PENDA: Programme for Evidence to Inform Disability Action
POInt: Process-outcome integration with theory
RCT: Randomised controlled trial
SDG: Sustainable development goals
ToC: Theory of change
UK: United Kingdom
US: United States
UPG: Ultra-poor graduation programme
VPRC: Village Poverty Reduction Committees
VSLA: Village Savings and Loans Associations
